# Efficacy and safety of bilateral continuous theta burst stimulation (cTBS) for the treatment of chronic tinnitus: design of a three-armed randomized controlled trial

**DOI:** 10.1186/1745-6215-10-74

**Published:** 2009-08-21

## Abstract

**Background:**

Tinnitus, the perception of sound and noise in absence of an auditory stimulus, has been shown to be associated with maladaptive neuronal reorganization and increased activity of the temporoparietal cortex. Transient modulation of tinnitus by repetitive transcranial magnetic stimulation (rTMS) indicated that these areas are critically involved in the pathophysiology of tinnitus and suggested new treatment strategies. However, the therapeutic efficacy of rTMS in tinnitus is still unclear, individual response is variable, and the optimal stimulation area disputable. Recently, continuous theta burst stimulation (cTBS) has been put forward as an effective rTMS protocol for the reduction of pathologically enhanced cortical excitability.

**Methods:**

48 patients with chronic subjective tinnitus will be included in this randomized, placebo controlled, three-arm trial. The treatment consists of two trains of cTBS applied bilaterally to the secondary auditory cortex, the temporoparietal associaction cortex, or to the lower occiput (sham condition) every working day for four weeks. Primary outcome measure is the change of tinnitus distress as quantified by the Tinnitus Questionnaire (TQ). Secondary outcome measures are tinnitus loudness and annoyance as well as tinnitus change during and after treatment. Audiologic and speech audiometric measurements will be performed to assess potential side effects. The aim of the present trail is to investigate effectiveness and safety of a four weeks cTBS treatment on chronic tinnitus and to compare two areas of stimulation. The results will contribute to clarify the therapeutic capacity of rTMS in tinnitus.

**Trial registration:**

The trial was registered with the clinical trials register of  (NCT00518024).

## Background

### Tinnitus

Tinnitus is the perception of sounds or noise in the absence of an external stimulus. About 10 to 15% of the general population [1] report this auditory phantom perception [2]. Around 1 to 2% of the patients are seriously impaired [1]. Sleep disturbances, depression, irritability, and anxiety symptoms are the most common psychiatric comorbidities of tinnitus [1,3]. Current therapies focus on the "management of tinnitus", i. e. they are a means to reduce tinnitus perception or awareness, and treating comorbidities rather than curing tinnitus itself [4-6]. Cognitive-behavioural therapies yield some relief [7], but are often not sufficient. To date, there is no pharmacological intervention or device available that has been proven to reliably reduce tinnitus. The pathophysiological causes of tinnitus are poorly understood which impedes the development of rational and evidence based therapies. However, recent findings indicate that chronic tinnitus is the result of maladaptive reorganization in the central auditory system [8] that can be reflected in hyperacitivity of cortical areas involved in the perception and processing of auditory information [6,9-14].

### Transcranial magnetic stimulation

Transcranial magnetic stimulation (TMS) is a non invasive method to depolarize cortical neurons based on the principle of electromagnetic induction [15]. Applying series of rapid consecutive single stimuli is called repetitive TMS (rTMS). Low frequency rTMS (1 Hz) has been shown to decrease the excitability of the motor cortex [16], whereas high frequency rTMS (≥ 5 Hz) produces the opposite effect [17]. rTMS causes activity changes in regions interconnected with the stimulated area through mono- or polysynaptic connections [18], modulates subcortical transmitter concentrations [19], and was shown to induce morphological modifications in stimulated areas as well as in areas linked to them [20]. Based on these findings, rTMS is used experimentally to treat a wide range of clinical disorders that may involve altered states of cortical excitability [21], such as major depression [22,23], auditory hallucinations [24], and stroke [25].

### TMS and tinnitus

Repetitive transcranial magnetic stimulation has recently been adopted to strengthen the concept of focally increased cortical excitability as a pathophysiological mechanism of tinnitus perception. Initially, it was shown that a high-frequency (10 Hz) rTMS induced 'virtual' lesion of temporoparietal cortical areas can transiently reduce tinnitus [26,27]. Further studies indicated that the effect size was negatively correlated with the tinnitus duration [28,29]. On the basis of these data, it has been proposed that a rTMS-induced reduction of hyperactivity of these cortical areas could yield beneficial effects for patients with chronic tinnitus [27]. To test this notion, low frequency rTMS was applied to areas of the temporoparietal cortex showing tinnitus-related hyperacitivity. Immediately after this intervention, tinnitus loudness was reduced for up to 30 min. The degree of reduction was dose dependent, and negatively correlated with tinnitus duration [11]. Several small clinical studies indicate that repeated application of low-frequency rTMS up to 2 weeks may have lasting ameliorating effects on chronic tinnitus [30-37]. However, the effect size was mostly moderate and interindividual responses as well as effect duration were highly variable. Further studies are needed to assess the clinical relevance of rTMS treatment in tinnitus and to identify the optimal stimulation paradigms as well as the most effective stimulation target site. Recently, continuous theta burst stimulation (cTBS) has been put forward as a modified rTMS paradigm [38] that reduces cortical excitability by applying three pulses at 50 Hz repeated every 200 ms over 40 s [38,39] at an intensity of 80% active motor threshold (AMT). For clinical purposes cTBS appears to be an applicable technique due to its low intensity, short duration, and similar efficacy [40]. In a first case report we demonstrated that cTBS is an effective approach to treat tinnitus [41].

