## Design and Methods

This randomised, placebo controlled study consists of 3 arms in a parallel design (Figure 1). Tinnitus distress, loudness and annoyance will be assessed before, during, and after 4 weeks of bilateral cTBS. Forty-eight patients will be randomised in an 1:1:1 ratio to either cTBS over the secondary auditory cortex (SAC), the temporoparietal association cortex (TAC) or sham stimulation (placebo: PLC).

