### Population

The patient population will consist of patients with a wide middle range of tinnitus duration and excluding those with an increased risk for adverse effect of TBS.

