#### Inclusion criteria

• Written informed consent

• Age: between 18 and 75 years

• Chronic tinnitus since at least 6 month, but not more than 5 years.

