### Data analysis

The geometric mean tinnitus score (TQ) in percent baseline will be compared between the three groups after the full treatment course of 4 weeks after the first stimulation, after 6 weeks, as well as 28 and 56 weeks after the first cTBS treatment in that prespecified order, as we expect effects sizes to have that order. If one group comparison is not statistically significant, the following comparisons are rated as not significant too. The confidence intervals for ratios of geometric means of tinnitus scores at 4 and 6 weeks will be computed from an analysis of variance (ANOVA) with factors *group *(SAC, TAC, PLC) and *time *(4 and 6 weeks) and the *group*time *interaction. Further ANOVAs of TQ with the between subject factor *group *will be carried out after 8, 28, and 56 weeks after the first treatment. Their residual variances are expected to differ. The longitudinal course of the stimulation effect will be described using all TQ measurements, including measurements at 2 and 16 weeks. Secondary efficacy measures will be analysed similarly. Only the tinnitus change cannot be divided by a baseline value and will be analysed by ordinal logistic regression as it is ordinal. The daily measurements on visual analog scales will be shown in diagrams. Confidence interval computations will assume normality of logit-transformed VAS. The routinely sampled safety data will all be plotted for each patient and will be used to quantify intensity and duration of adverse effects should such occur. Data analysis will be performed in the Department of Medical Biometry of University Hospital of Tübingen using JMP 7.0 (SAS Institute Inc.) after imputation with SPSS 17.0 (SPSS Inc.).

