### Randomization

A randomisation list was prepared by the Department of Medical Biometry of University Hospital of Tübingen (RV) using permuted blocks. Allocations were concealed in opaque sealed envelopes, that are opened by a third person immediately prior to the first treatment.

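### Tinnitus duration, which the protocol itself names as a predictor of TMS response, is left out of the prespecified TQ models, at a cost in precision and in protection against chance imbalance, mainly for SAC versus TAC

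*Protocol article*

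**What the plan says.** The protocol article links duration to response twice under TMS and tinnitus. After the high-frequency studies it says "Further studies indicated that the effect size was negatively correlated with the tinnitus duration". For low-frequency rTMS it says "The degree of reduction was dose dependent, and negatively correlated with tinnitus duration". It names no other patient characteristic as a predictor of response.

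Population describes the sample as "patients with a wide middle range of tinnitus duration", and Inclusion criteria sets the limits: "Chronic tinnitus since at least 6 month, but not more than 5 years".

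Data analysis spells out the models. The confidence intervals at 4 and 6 weeks "will be computed from an analysis of variance (ANOVA) with factors" group and time, plus their interaction. For later visits, "Further ANOVAs of TQ with the between subject factor *group *will be carried out after 8, 28, and 56 weeks after the first treatment". TQ is expressed relative to its own baseline, but duration appears in no model.

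**The concern.** The protocol gives a reason to expect response to vary with duration, enrols a wide range of durations, and then fixes a model that ignores them. This is a stated list of model factors, not a gap that a fuller document would be expected to fill. Dividing by baseline TQ does not supply the missing information, because baseline distress is a different variable from duration.

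With 16 patients per arm, mean duration will often differ noticeably between arms. If shorter duration goes with better response, the arm that draws shorter durations will look better than it should. The comparison of the two stimulation sites is the most exposed: both arms are active, so duration can act in both, and an imbalance can imitate or hide a site difference. The Discussion says the site found best here will feed into the design of a larger trial. Variance that duration could explain also stays in the error term.

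**Working it through.** **Inputs from the article.** 48 patients ("Forty-eight patients will be randomised in an 1:1:1 ratio"), so 16 per arm; SD of the log TQ ratio 0.18; target effect 0.19; local level 0.017 and local power 0.93 (Sample size calculation); duration 6 to 60 months (Inclusion criteria).

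**Assumed, because the article does not give them.** The correlation r between log duration and log TQ ratio, taken as 0.2 to 0.6; duration spread evenly on the log scale; two-sided tests.

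**1. The plan's own figures.** The effect reproduces: ln(0.97/0.80) = 0.193. The stated local power does not. With 16 per arm, effect 0.19, SD 0.18 and level 0.017, two-sided power is about 0.69 (non-central t, 45 df) or 0.73 (normal approximation). That is a separate matter, but it makes about 0.70 the starting point for step 5.

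**2. How often the arms differ in duration.** The SD of a difference between two arm means, in units of the SD of log duration, is sqrt(2/16) = 0.354.
- P(a given pair differs by more than 0.5 SD) = 2 × [1 − Φ(0.5/0.354)] = 0.16.
- P(a given pair differs by more than 1 SD) = 0.005.
- P(at least one of the three pairs differs by more than 0.5 SD) = 0.33, by simulation.

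With an even spread on the log scale, the SD of log duration is ln(10)/sqrt(12) = 0.665. Half an SD is then a ratio of exp(0.332) = 1.39 in geometric mean duration.

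**3. What a 0.5 SD imbalance does to a contrast.** Shift = 0.5 × r × 0.18, for a contrast whose two arms both depend on duration.

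| r | Shift (log units) | Share of 0.19 |
|---|---|---|
| 0.2 | 0.018 | 9% |
| 0.3 | 0.027 | 14% |
| 0.4 | 0.036 | 19% |
| 0.5 | 0.045 | 24% |
| 0.6 | 0.054 | 28% |

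For scale, the standard error of one contrast is 0.18 × sqrt(2/16) = 0.064, and significance at 0.017 two-sided needs a difference of about 0.158. At r = 0.4 the shift is 0.036/0.064 = 0.57 standard errors.

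**4. Type I error of the unadjusted test.** Two arms with no true difference, duration acting equally in both, nominal level 0.017, by simulation:

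| | r = 0.3 | r = 0.5 |
|---|---|---|
| Over all randomisations | 0.017 | 0.017 |
| Imbalance below 0.1 SD | 0.013 | 0.007 |
| Imbalance about 0.5 SD | 0.020 | 0.028 |
| Imbalance about 1 SD | 0.05 | 0.12 |

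The level holds on average. It is off once the imbalance is known, in both directions.

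**5. What the covariate recovers.** Local power against sham at 16 per arm, by simulation with effect 0.193, level 0.05/3 and one common slope for log duration. Without the covariate it is about 0.70.

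| r | Only the active arms depend on duration | All arms depend on duration |
|---|---|---|
| 0 | about 0.69 | about 0.69 |
| 0.3 | 0.71 | 0.74 |
| 0.4 | 0.72 | 0.77 |
| 0.5 | 0.74 | 0.83 |

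The r = 0 row shows the price of a useless covariate: about 0.01.

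**The case against.** **The planned analysis is valid.** Randomisation already builds chance imbalance into the error rate, and step 4 confirms it. This stands, so leaving duration out is an inefficiency and not an error. It covers the arms as randomised; the efficacy analysis uses patients treated per protocol, where later exclusions make the argument somewhat weaker.

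**A reader might infer that imbalance could pass for a treatment effect against sham.** The article does not support that. It describes duration as correlated with the effect of TMS, that is, as an effect modifier. If that is all it is, imbalance can enlarge or shrink a real active-versus-sham effect but cannot create one where none exists.

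**A reader might also infer that the randomisation is unstratified and should be changed.** Randomization says only that the list was prepared "using permuted blocks". Strata are commonly left to the full protocol, so a condensed article's silence shows nothing.

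**The evidence is indirect.** The correlations are reported for a transient high-frequency effect and for loudness reduced for up to 30 minutes after low-frequency rTMS, not for TQ distress after four weeks of cTBS. For the repeated-treatment studies the article mentions variable response but no link with duration. The five-year cap already removes the longest durations. This stands, and it is why r is an assumption and may be near zero.

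**The gains are modest.** At r = 0.3 in the active arms only, power moves by about 0.01. A common slope is also not quite the right model if duration has no effect under sham. Both are fair. The case rests on the low cost and on the site comparison, not on a large gain in power.

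**Conclusion.** The point holds as a recommended improvement to a stated analysis, not as a flaw that invalidates it. The protocol names duration as a predictor, admits a tenfold range, and omits it from every TQ model. The loss is in precision and in protection against conditional bias, chiefly for SAC versus TAC. In about one randomisation in six a given pair of arms differs by more than 0.5 SD in mean log duration, and a difference of 0.5 SD moves a contrast by 9 to 28% of the target effect. That range depends wholly on the assumed r of 0.2 to 0.6. If duration does not predict four-week TQ change, nothing is lost by the present plan. Adjustment would not close the gap between about 0.70 and the stated local power of 0.93 at any r shown in step 5.

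**What to change.** In Data analysis, add centred log tinnitus duration as a prespecified covariate in every TQ model: the 4- and 6-week ANOVA and each later ANOVA. Base the SAC/PLC, TAC/PLC and SAC/TAC ratios of geometric means on the adjusted means. Report the group-by-duration interaction as a supporting analysis only. Settle this before unblinding, since adjusting after an imbalance has been seen would be data-driven.

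Duration has to be established at the eligibility check, so no new visit or measurement is needed; the value itself should be recorded, not only whether the criterion is met. The cost is one degree of freedom in the main model, two more in the supporting model, and about 0.01 of local power if duration turns out not to predict TQ change. No change to the randomisation is asked for.

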### Objectives

We hypothesize that compared to sham stimulation cTBS can induce a distinctive attenuation of tinnitus distress and loudness and thus be of therapeutic value. Further aims of the study are:

• To compare the effect of cTBS on the secondary auditory cortex with its effect on the temporoparietal association cortex.

• Assessment of safety in terms of impairment in audiologic and speech-audiometric measures as well as the documentation of other unwanted side effects.

## Design and Methods

This randomised, placebo controlled study consists of 3 arms in a parallel design (Figure 1). Tinnitus distress, loudness and annoyance will be assessed before, during, and after 4 weeks of bilateral cTBS. Forty-eight patients will be randomised in an 1:1:1 ratio to either cTBS over the secondary auditory cortex (SAC), the temporoparietal association cortex (TAC) or sham stimulation (placebo: PLC).

**Figure 1 F1:**
[figure not shown]
**Study Design**.

### Population

The patient population will consist of patients with a wide middle range of tinnitus duration and excluding those with an increased risk for adverse effect of TBS.

#### Inclusion criteria

• Written informed consent

• Age: between 18 and 75 years

• Chronic tinnitus since at least 6 month, but not more than 5 years.

#### Exclusion criteria

• Objective tinnitus

• Acute or chronic inflammation of the middle ear, acute hearing loss, hearing loss due to an acoustic trauma within less than past 6 weeks

• Morbus Menière or fluctuating hearing loss

• Epilepsy

• Brain trauma

• Brain surgery

• Heart pacemaker

• Intake of anticonvulsants, antipsychotics, and regular intake of benzodiazepin

• Suicidality

• Other severe pathological chronic condition that might confound treatment effects or interpretation of data

• Pregnancy

• Participation in another clinical study regarding tinnitus within the past 3 months and during enrolment in our study.

#### Data sets

For evaluation of security all data gathered will be used and analyzed as treated. The analysis of the efficacy measures, especially with respect to the stimulus placement, requires a concentration on patients treated per protocol (PP). Missing observations are imputed using a full conditional Markov-Chain Monte Carlo method for variables with more than 75% valid values. An exploratory analysis of all dependent variables by the randomised treatment, i. e. the mere intention to treat (ITT), will be conducted to plan subsequent confirmatory studies.

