### Outcome measures

The primary efficacy measure in the present study is the change of the tinnitus distress as measured by the TQ [45] after 4 weeks of cTBS. The TQ [45]), originally developed by Hallam et al. [49], is the most widely used, well validated and reliable inventory [50] to quantify tinnitus ditress available in German language [30,32,34,41,51-58]. It comprises 52 multi-scaled items in order to assess emotional and cognitive handicaps, penetrance of the tinnitus, hearing problems, sleep disturbances, and somatic discomfort. The TQ was used in pharmacological, behavioural and TMS studies. Pharmacological studies did not yield therapeutic effects [58,59]. Behavioural therapy yield effect sizes between 6 and 28% on the TQ [60,61]. Pilot rTMS studies reported effects sizes between 5 and 25% [34,41,52].

Secondary efficacy variables are tinnitus change [46] and the changes in BDI [47] and in the VAS for tinnitus loudness and tinnitus annoyance [46,62].

Changes regarding psychopathology will be measured using the SCL-90R [48]. Feasibility of the study will be assessed and reported together with the results.

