### Withdrawal from the study

In case of endangerment of personal security or lack of compliance or withdrawal of informed consent, a patient will instantly be excluded from further participation in the study.

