## Discussion

The available data on the efficacy of tinnitus treatment with rTMS is incomplete [30-37]. The effect size, the clinical relevance and the optimal stimulation parameters are virtually unknown. This placebo-controlled phase II clinical trial has been designed to investigate the efficacy of a 4 weeks treatment with bilateral cTBS on chronic tinnitus and to compare the effectiveness of two different stimulation areas. Since the laterality of tinnitus-related cortical hyperactivity and rTMS effects in mono- and bilateral tinnitus have been shown to be interindividually variable [11,64], we opted for a bilateral cTBS. Recent studies on therapeutic efficacy of rTMS in major depression pointing towards a superior effectiveness of longer treatment durations [23] prompted us to extend cTBS treatment to 4 weeks. Moreover, against the background of a dose dependency of rTMS effects in tinnitus [11] and in order to assure a sufficient dose of stimulation, the patients will receive two stimulation trains on each side. Hence, bilateral, long-term application of cTBS to two different cortical sites will provide comprehensive data for an evaluation of the clinical relevance of TMS treatment in chronic tinnitus and an improvement of treatment parameters. Based on the effect size and standard deviation of the Intention-to-Treat analysis as well as on the finding of the optimal stimulation localization a larger clinical efficacy study will be designed.

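### The formal comparison with sham is made on per-protocol patients, with intention to treat only exploratory, so its stated error level is not assured

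*Protocol article*

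**What the plan says.** The Objectives section of the protocol article sets a superiority hypothesis: "We hypothesize that compared to sham stimulation cTBS can induce a distinctive attenuation of tinnitus distress and loudness". Under Outcome measures the primary endpoint is "the change of the tinnitus distress as measured by the TQ [45] after 4 weeks of cTBS".

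The Data sets section fixes who is analysed. For efficacy: "The analysis of the efficacy measures, especially with respect to the stimulus placement, requires a concentration on patients treated per protocol (PP". For the randomised groups: "An exploratory analysis of all dependent variables by the randomised treatment, i. e. the mere intention to treat (ITT), will be conducted", with the purpose of planning later confirmatory studies. On missing data: "Missing observations are imputed using a full conditional Markov-Chain Monte Carlo method for variables with more than 75% valid values". Safety is analysed as treated. No other section makes intention to treat (ITT) primary or co-primary.

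Sample size calculation and Data analysis attach formal inference to the efficacy comparisons. There are three pairwise tests at a local level of 0.017, intended to hold a multiple level of 0.05, and a fixed order over time points.

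Withdrawal from the study supplies a way out after randomisation. Besides danger to the patient it names "lack of compliance or withdrawal of informed consent, a patient will instantly be excluded from further participation in the study".

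The Discussion calls the trial phase II and says a larger trial will be designed "Based on the effect size and standard deviation of the Intention-to-Treat analysis" and on the finding about the best site.

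**The concern.** A significance level for a treatment comparison relies on the groups being alike except for treatment and chance. Randomisation secures that for everyone randomised. It does not secure it for a subset chosen by what happened afterwards. Here the subset is the per-protocol (PP) set, and the exits named in the article (safety, compliance, consent) can each be connected with how a patient tolerates a four-week daily course or how much benefit is felt.

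The one reason given for PP is stimulus placement. It bears on whether one stimulated area works better than the other, where a patient stimulated at the wrong place is uninformative. It does not bear in the same way on whether assignment to cTBS does better than assignment to sham.

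At stake is whether a significant PP result against sham could be read at the stated multiple level of 0.05. With 16 patients per arm, one to three exclusions are enough to matter if they are related to outcome.

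**Working it through.** **Inputs from the article.** SD of the log ratio to baseline 0.18; planned effect 0.19 log units; local level 0.017; 16 patients per arm, three arms (all from Sample size calculation). Sidedness is not stated; two-sided is assumed here. The planned effect reproduces: ln(0.97/0.80) = 0.193, or 0.19 as printed.

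**Inputs the article does not give.** It gives no number of PP exclusions, no pattern by arm and no link with outcome. It states no figure for this point that could be reproduced. What follows is therefore a set of scenarios, not an estimate.

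**Step 1: spurious shift.** Assume no true effect, and remove the k patients with the highest log ratios (worst responders) from one arm of 16. The mean of those who remain moves by

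shift = −SD × (sum of the k largest expected standard normal order statistics) ÷ (16 − k).

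For n = 16 the three largest expected values are about 1.77, 1.28 and 0.99.

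- k = 1: 0.18 × 1.77 ÷ 15 = 0.021
- k = 2: 0.18 × (1.77 + 1.28) ÷ 14 = 0.039
- k = 3: 0.18 × (1.77 + 1.28 + 0.99) ÷ 13 = 0.056

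Against the planned effect these are 0.021/0.19 = 11%, 0.039/0.19 = 21% and 0.056/0.19 = 29%.

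**Step 2: error rate.** Simulated null trials (100,000 or more per scenario), t test at 0.017 two-sided with the three-group residual:

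| Patients lost (worst responders) | Shift, log units | Result |
|---|---|---|
| 1, 2, 3 from one active arm | 0.021, 0.039, 0.056 favouring cTBS | two-sided error about 0.023, 0.040, 0.066 |
| 1, 2, 3 from sham | 0.021, 0.039, 0.056 against cTBS | false positives favouring cTBS fall from about 0.008 to 0.004, 0.002, 0.001 |
| 1, 2, 3 from both arms | none | false positives favouring cTBS about 0.010, 0.012, 0.013 |
| any number, unrelated to outcome | none | nominal |

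The first row varies a little between runs and with the choice of residual: 0.023 to 0.026 for one patient and 0.040 to 0.041 for two. In the third row the error rises slightly without any shift, because cutting off one tail also shrinks the residual SD.

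**Step 3: weaker selection.** Suppose two patients leave each arm, at random from sham and, in the active arm, by a marker correlated 0.5 with poor outcome. The shift is then 0.020, and false positives favouring cTBS go from 0.0085 to about 0.018. With four leaving each arm they reach about 0.030.

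**Step 4: what ITT would cost.** Suppose a share q of each active arm is off protocol and responds like sham. At 16 per arm, SD 0.18 and two-sided 0.017 (normal approximation), the diluted effect is 0.19 × (1 − q). Power per comparison is 0.73 at q = 0, 0.62 at q = 10% and 0.50 at q = 20%. The PP analysis loses patients instead: 16 × 0.9 = 14.4 per arm gives 0.67, and 16 × 0.8 = 12.8 gives 0.61. At these shares the power lost by moving from PP to ITT is about 0.05 and 0.11.

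**The case against.** The best defence is the setting. This is a phase II trial, the PP choice is disclosed with a reason, an ITT analysis of every dependent variable is also planned, and confirmation is left to a later trial. The article never calls its own tests confirmatory, and a reader who does so goes beyond the text. This lowers the weight of the point. It does not remove it, because the article still states superiority over sham and controls the multiple level for it.

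Three stronger readings are tempting and not supported.

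- **That PP favours cTBS.** The Blinding section designs sham to match the noise and the unpleasant sensation, so greater intolerance in the active arms is not established. If lack of felt benefit drives exits, sham patients could leave at least as often, which works against cTBS.
- **That the one-arm figures are a ceiling.** They are the extreme case only for k losses from a single arm. Losing good responders from sham as well would exceed them.
- **That the Discussion shows the authors trust ITT over PP.** Sizing a later trial from the ITT effect and SD is ordinary planning. It does not say which estimate they regard as valid here.

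It is also fair that the article does not define PP. If it chiefly means stimulated at the intended place, exclusions may have little to do with response. The definition may stand in the full protocol, which is not shown, so its absence is no criticism. Nor does imputation answer the point: it fills missing values, and the article does not say that it returns excluded patients to the efficacy set.

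**Conclusion.** The point holds in this form: the formal tests against sham fall on a set chosen after randomisation, the reason given does not cover that comparison, and the multiple level of 0.05 is therefore not assured. The direction of any bias is open, and its size cannot be derived from the article. The illustrations show only that one to three outcome-related exclusions from one arm of 16 could produce a shift of 11% to 29% of the planned effect and raise the local error from 0.017 to as much as about 0.066. If exclusions are few or unrelated to outcome, the harm is small or nil.

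This rests on a two-sided test, SD 0.18, full enrolment of 16 per arm and assumed exclusion patterns. Whether 16 per arm is enough, with or without exclusions, is a separate question and adds nothing to the weight of this one. Given the phase II setting, the change should be made but is not a bar to the trial.

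**What to change.** In Data sets, make ITT (all randomised patients, in the arm assigned) the primary analysis of the TQ at 4 weeks and of the later time points in the stated order. Keep PP as a supportive analysis, mainly for the comparison of the two stimulation sites, and as-treated for safety.

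State how patients who stop enter the ITT set. Where consent allows, go on collecting the TQ after treatment stops; Withdrawal from the study, which now ends participation at once, needs matching wording. Apply the planned imputation to what is still missing. The 75% rule limits this: with 48 randomised, 0.75 × 48 = 36, so at least 37 TQ values are needed at a time point. The plan should say what is done if a late visit falls short.

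Cost: both analyses are already planned, so the statistical change is one of order and wording. The real costs are the extra follow-up of patients who stop, dilution of the effect if non-compliance is common, and reliance on imputed values for those who withdraw consent, which will not repair losses that depend on the unseen outcome.
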